### Randomization and blinding

Randomization of trial participants will be based on computer-generated random numbers prior to surgery. The random numbers will be printed and placed in consecutively numbered and separate sealed opaque envelopes, which will be opened only when a patient is enrolled and meets all inclusion criteria. The principal doctor (CL) will assign the participant to a group on the basis of the number. The research assistant should receive the notification in a timely fashion and assign patients to their study group strictly as required. This study will be single-blind. The participants will be blinded to the allocation of the participants, whereas the investigators and project manager will be unblinded. If an unexpected emergency occurs, allocation will be disclosed to the investigators, the participant will be withdrawn from this study, and a detailed explanation will be recorded if unblinding happens.

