### Study dropouts

All recruited participants have the right to quit this study at any time for any reason based on the ethical consideration without any negative effects on their further therapy. Meanwhile, all researchers have the right to terminate the enrollment of any patients at any time within reasonable circumstances. All changes and reasons will be recorded immediately in the case report form (CRF). If the dropout rate is higher than 10%, we will apply multiple imputation to avoid pitfalls involved with listwise deletion of cases. The intention-to-treat principle will be applied to analyze the data.

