#### Complications

Some postoperative complications, such as bleeding, pain at the incision site, postoperative air leak, prolonged air leak, and atelectasis, will be treated in accordance with clinical guidelines. During every ward round, conducted at least twice a day, the doctors in charge will solicit the patients’ feedback and perform specific physical examinations to monitor any adverse events. All adverse events will be recorded in a timely fashion in the CRF. Postoperative follow-up will be conducted for all participants. Participants with any serious harm experienced as a result of trial participation will receive adequate compensation.

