#### Primary and secondary outcomes

All outcomes will be defined in accordance with two previous studies [17, 18]. The primary outcomes are the levels of leukocytes, neutrophils, and inflammatory factors—interleukin-1β (IL-1β), IL-6, IL-8, IL-2, tumor necrosis factor-alpha (TNF-α), C-reactive protein (CRP), prostaglandin E_2_ (PGE_2_), and 5-hydroxytryptamine (5-HT)—on the first postoperative day. On the first postoperative morning, a trained nurse will collect blood samples and then send samples to test. The mean difference of the levels of leukocytes, neutrophils, and inflammatory factors will be compared between the two groups.

The secondary outcomes are (i) the levels of leukocytes, neutrophils, and inflammatory factors (IL-1β, IL-6, IL-8, IL-2, TNF-α, CRP, PGE_2_, and 5-HT) on the second and third postoperative days; (ii) the incidence of postoperative fever on the first, second, and third postoperative days; (iii) the volumes of chest drainage within the first 3 operative days, the duration of drainage, and postoperative hospitalization; and (iv) the incidence of postoperative complications (incision infection, pain, atelectasis, hemorrhage, etc.) and the incidence of pleural effusion requiring thoracic puncture or drainage within 30 days after surgery.

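### The emergency clause withdraws participants from the study, which contradicts intention to treat and follow-up of all participants; if it governs, 30-day complications could be under-counted

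*Protocol article*

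**What the plan says.** Randomization and blinding sets the rule for an unexpected emergency: "allocation will be disclosed to the investigators, the participant will be withdrawn from this study, and a detailed explanation will be recorded". The sentence attaches that explanation to the case of unblinding. Just before it, the same section describes a trial in which participants are blinded, "whereas the investigators and project manager will be unblinded".

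Three other statements point the other way:

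- Study dropouts: "The intention-to-treat principle will be applied to analyze the data". The same section brings in multiple imputation only if dropout exceeds 10%.
- Complications, on safety recording: "All adverse events will be recorded in a timely fashion in the CRF".
- Complications, on what happens after surgery: "Postoperative follow-up will be conducted for all participants".

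Secondary outcome (iv) is the most exposed. One part of it is "the incidence of pleural effusion requiring thoracic puncture or drainage within 30 days after surgery". Its other part is a broader count, worded as "the incidence of postoperative complications (incision infection, pain, atelectasis, hemorrhage, etc".

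**The concern.** The clause removes the participant from the study, not only from a treatment. Under Intervention, each group has one lavage before the chest is closed, so after surgery no trial treatment remains to be stopped. Disclosing the allocation to investigators who already know it adds nothing. What is left is the removal of a correctly randomised patient because of something that happened after randomisation.

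If that is how the clause is applied, data are missing because of the patient's course. The patients affected are ones that the safety analysis and the 30-day complication outcome need to keep. The loss may differ between arms. Imputation is a weak remedy, because filling in values from patients without an emergency assumes that the two kinds of patient are alike. An emergency before the first postoperative morning could also cost that patient's primary blood markers.

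**Working it through.** **The plan's own figure.** The article gives no emergency or complication rate, so it has no figure on this point to reproduce. Its one calculated result is the power for day-1 leukocytes. With 200 × 0.9 = 180 per group, effect size 0.5 and two-sided 5%, the noncentral t distribution gives 0.9972. This matches the stated 99.72%, and the present point does not affect it.

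**Which text governs.** Three readings are possible:

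1. The withdrawal clause governs completely: the patient leaves both numerator and denominator.
2. The event is recorded under Complications, but the patient then leaves: that event is counted, while later complications, drainage and stay may be lost.
3. The follow-up and intention-to-treat statements govern: nothing is lost.

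No section chooses among them.

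**Size under reading 1, by assumption.** Let p be the true complication proportion and f the proportion with an emergency. Assume that every emergency is a complication and that those patients are dropped. Then

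observed proportion = (p − f) / (1 − f).

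Per arm of 200 (2% is 4 patients, 5% is 10):

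| True p | f = 2% | f = 5% |
|---|---|---|
| 10% (20/200) | 16/196 = 8.2% | 10/190 = 5.3% |
| 20% (40/200) | 36/196 = 18.4% | 30/190 = 15.8% |
| 30% (60/200) | 56/196 = 28.6% | 50/190 = 26.3% |

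**Difference between arms.** Assume other complications at 15% (30 of 200) in both arms, and vary the emergencies:

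| Emergencies, one arm vs the other | True difference | Observed difference |
|---|---|---|
| 2% vs 2% | 0 | 0 |
| 4% vs 2% | 38/200 − 34/200 = 2.0 points | 30/192 − 30/196 = 15.6% − 15.3% = 0.3 points |
| 6% vs 2% | 42/200 − 34/200 = 4.0 points | 30/188 − 30/196 = 16.0% − 15.3% = 0.7 points |

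In these cases the whole true difference comes from the emergencies, so nearly all of it vanishes by construction. If f is the same in both arms, a difference in p is only rescaled: (p₁ − p₂)/(1 − f), a factor of 1/0.98 = 1.02 or 1/0.95 = 1.05. Material distortion of the comparison therefore needs emergencies that differ by arm.

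**Imputation.** The 10% trigger is 0.10 × 400 = 40 patients. Emergencies at 2% or 5% of 400 are 8 or 20 patients, so on their own they would not reach it.

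**The case against.** The strongest reply is that the article never says follow-up stops or data are discarded. Complications promises that adverse events are recorded and that everyone is followed, doctors see patients at least twice a day, and intention to treat points to keeping withdrawn patients in the analysis. The clause sits in the blinding section, reads like a standard emergency-unblinding provision, and does not define its trigger. The article treats bleeding, air leak and atelectasis as complications to be managed, without mentioning withdrawal. A condensed article may also leave the handling of withdrawn patients to the full protocol.

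Much of this stands. A reader might infer that the patients with the most serious events certainly leave safety follow-up, that 30-day complications are under-counted as a fact, and that most of a safety signal would disappear. The documents do not support that. The trigger is undefined, so it is not shown to cover the most serious events. Other text, if followed, prevents the loss. A near-total loss of signal appears only when the emergencies are assumed both to be unbalanced and to carry the entire difference.

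There is also overlap. Exclusion criteria (viii) and (ix) already remove patients for defined intraoperative accidents and for bleeding or air leak that needs reoperation. The additional loss from this clause alone is unknown and may be small.

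The reply does not remove the contradiction. The withdrawal wording is mandatory and specific to the event, whereas the follow-up statement is general, and a withdrawn person may no longer count as a participant. This is a stated rule that conflicts with other stated rules. It is not a detail left to another document.

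**Conclusion.** The point holds as a contradiction with conditional consequences. The emergency clause cannot be squared with intention to treat and follow-up of all participants, and the article does not say which prevails. If the clause governs, randomised patients leave because of a post-randomisation event, and the 30-day complication results can be biased. If the other statements govern, there is no under-count.

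The size cannot be derived from the documents. Under the assumptions shown, the observed rate falls short of a true 20% by 1.6 points with 2% emergencies (20 − 18.4) and by 4.2 points with 5% (20 − 15.8). The comparison between arms is materially distorted only if emergencies differ by arm. The main exposure is secondary outcome (iv) and the safety analysis, with drainage and stay also affected. The primary markers are touched only by emergencies before the first-morning sample, and the power figure is unchanged.

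**What to change.** Reconcile Randomization and blinding with Study dropouts and Complications by replacing the withdrawal clause. Suggested content: an emergency, or disclosure of the allocation, does not by itself end data collection; the participant stays in follow-up to day 30 where feasible and is analysed in the assigned group, unless consent to data collection is withdrawn. The requirement to record an explanation can stay.

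This concerns data retention only. It changes nothing about clinical care and need not touch the researchers' separate right, under Study dropouts, to terminate a patient's enrolment.

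The cost is one amended sentence, ethics committee agreement under Protocol amendments, and a few more follow-up records. Trial status says that recruitment has not opened, so the change can be made before any data are affected.

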### Sample size

This is the first study that focuses on the effect of different volume of pleural lavage on the clinical outcomes following VATS lobectomy and MLND, and no reference is available to estimate the sample size. We estimated the power on the basis of the Student’s *t* test of the levels of leukocytes on the first postoperative day in each group. We estimate an effect size of 0.5 from our experience. A total of 400 participants will be recruited in this study (200 in each group). Judging from our experience, we set the dropout rate at 10% to account for inability to complete the treatment, data errors, loss to follow-up, and other unanticipated study problems. Given a type I error rate of 5%, this study could provide a power of 99.72% by using G*Power (software version 3.1.3, University of Düsseldorf, Germany).

### Intervention

A total of 400 NSCLC patients who are 18 to 75 years of age and who are undergoing VATS lobectomy and MLND will be recruited in our study on the basis of the inclusion and exclusion criteria. The patients will be divided into two groups:

#### Group A (experimental group): 500 mL pleural lavage fluid

Before closing the chest wall, we will perform careful hemostasis and then flush the thoracic cavity with 500 mL 0.9% sodium chloride injection at 38–40 °C. A 28-F catheter will be indwelled for chest drainage.

#### Group B (experimental group): 3000 mL pleural lavage fluid

We will use 3000 mL 0.9% sodium chloride injection at 38–40 °C to flush the thoracic cavity in this group. All other procedures are the same as those of group A.

### Study dropouts

All recruited participants have the right to quit this study at any time for any reason based on the ethical consideration without any negative effects on their further therapy. Meanwhile, all researchers have the right to terminate the enrollment of any patients at any time within reasonable circumstances. All changes and reasons will be recorded immediately in the case report form (CRF). If the dropout rate is higher than 10%, we will apply multiple imputation to avoid pitfalls involved with listwise deletion of cases. The intention-to-treat principle will be applied to analyze the data.

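### Researchers, including unblinded investigators, may end any participant's enrolment at any time on undefined grounds; after the lavage this can only cost outcome data, and the intention-to-treat sentence does not replace data that are not collected.

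*Protocol article*

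**What the plan says.** Study dropouts gives participants the right to leave and then adds a second right: "all researchers have the right to terminate the enrollment of any patients at any time within reasonable circumstances". The circumstances are not described and no time limit is set. Changes and reasons go into the case report form. On missing data the section says: "If the dropout rate is higher than 10%, we will apply multiple imputation to avoid pitfalls involved with listwise deletion of cases". It closes with: "The intention-to-treat principle will be applied to analyze the data".

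Randomization and blinding says that participants are blinded, "whereas the investigators and project manager will be unblinded". After an emergency disclosure of allocation, "the participant will be withdrawn from this study, and a detailed explanation will be recorded if unblinding happens".

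The study treatment is a single act before chest closure. In group A the surgeons "flush the thoracic cavity with 500 mL 0.9% sodium chloride injection at 38–40 °C"; group B differs only in volume (3000 mL). No later study treatment is described. The primary outcomes are blood markers on the first postoperative morning. Secondary outcomes cover days 2 and 3, drainage and hospital stay, and events up to day 30 (Primary and secondary outcomes).

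**The concern.** Investigator withdrawal normally exists so that a continuing treatment can be stopped. Here randomisation takes place before surgery, so the right has a use until the lavage is done. From chest closure onward nothing remains to be stopped, and ending a patient's enrolment can only end the collection of outcomes.

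The investigators who may use this right know the arm and see the patient daily. If a difficult course makes termination more likely, and that judgement differs between arms, the patients who remain are no longer comparable, however sound the randomisation was. An intention-to-treat analysis can place patients in their assigned arm, but it cannot supply values that were never measured. This is an objection to a rule that the article sets out, not to a detail that it leaves to another document.

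**Working it through.** **1. The plan's own figure.** Inputs from Sample size: standardised effect 0.5, 200 per arm, 10% dropout, type I error 5%. With 200 × 0.9 = 180 per arm, a two-sided two-sample t test (noncentral t) has power 99.72%, exactly as stated. The power figure is not in dispute. It does show that a 10% loss was treated purely as a loss of numbers.

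**2. Which outcomes are exposed.**
- Day-1 markers: a termination before the first-morning sample means that no value exists, but nobody has yet seen the marker, so selection on it can only be indirect. A termination after the result is in the electronic chart matters only if the value is then dropped.
- Days 2 and 3, drainage, hospital stay, 30-day events: a termination can come after the clinical course and the day-1 result are known, and before these outcomes are complete. These are the most exposed.

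**3. Whether the missing-data rule would act.** Take 20 patients lost from one arm. That is 20/400 = 5% of the trial, or 20/200 = 10% of the arm. Neither is higher than 10%, so imputation is not triggered under either reading.

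**4. Illustrative size.** Assumptions not in the document: no true effect; outcome with SD 1; removal from one arm only; the removed patients average m SD above the mean; their values are not analysed. If a fraction p of the arm is removed, the mean of the rest shifts by p·m/(1 − p). The standard error is √(1/n₁ + 1/200), where n₁ is the number left. Rejection rates are for a two-sided 5% t test.

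| Removed | m | Shift (SD) | Standard error | Shift / SE | Type I error |
|---|---|---|---|---|---|
| 10 of 200 | 1.0 | 0.05/0.95 = 0.053 | 0.101 | 0.52 | 8.1% |
| 20 of 200 | 1.0 | 0.10/0.90 = 0.111 | 0.103 | 1.08 | 19.0% |
| 10 of 200 | 1.5 | 0.075/0.95 = 0.079 | 0.101 | 0.78 | 12.2% |
| 20 of 200 | 1.5 | 0.15/0.90 = 0.167 | 0.103 | 1.62 | 36.6% |

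Hand check of the second row by the normal approximation: P(Z > 1.96 − 1.08) + P(Z < −1.96 − 1.08) ≈ 0.189 + 0.001 = 0.19.

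**5. A second model.** In a simulation, patients were removed from one arm on a score with correlation r to the outcome. With 20 removed, type I error was about 9% at r = 0.3, 17% at r = 0.5, and 52% in the extreme case r = 1. With 10 removed it was about 6.5%, 8.7% and 20%. At r = 0 it stayed near 5% (simulated 5.4% and 5.7%). The two models agree: at r = 0.5 the simulated shift for 20 removals was 0.096 SD, which corresponds to m = 0.096 × 0.9/0.1 ≈ 0.87.

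**6. Removal from both arms.** If 20 leave one arm and 10 the other, both at +1 SD, the net shift is 0.111 − 0.053 = 0.058 SD. The standard error is √(1/180 + 1/190) = 0.104, the ratio 0.56, and the type I error about 9%.

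**7. Effect on a true difference.** At the design effect of 0.5 SD, a shift of 0.111 leaves (0.5 − 0.111)/0.103 ≈ 3.8 standard errors and power near 97%; a shift of 0.167 leaves about 90%. For a smaller true effect of 0.3 SD (assumed), simulated power falls from about 85% to 65% (r = 0.3) or 54% (r = 0.5) with 20 removed.

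**The case against.** The sentence may be routine text that is rarely used, and the article contains safeguards. Reasons must be recorded. A three-member committee supervises adherence and checks the case report form against original data, and the ethics committee monitors as well (Data management). Laboratory technicians and statisticians are blinded. The section on Complications plans postoperative follow-up for all participants.

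A reader might infer several stronger things that the documents do not support:
- *That recorded day-1 values are thrown away.* Nothing says so. A value already in the chart can be analysed as assigned, and the intention-to-treat sentence points that way.
- *That the protocol excludes every dropout when dropout is 10% or less.* This is implied by the imputation trigger and its reference to listwise deletion; it is not stated.
- *That everyone who may terminate a patient knows the arm.* The unblinded roles are the investigators and the project manager; researchers as a whole include blinded staff.
- *That the rule would hide the effect the trial is designed for.* At 0.5 SD power stays at about 90% or more in the +1 and +1.5 SD scenarios.

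These points limit the concern but do not remove it. Recording a reason documents a removal without preventing it. A committee that checks adherence cannot object to what the protocol permits. Blinded laboratory staff and statisticians do not decide who stays. The follow-up sentence does not say that it covers patients whose enrolment has been ended. Multiple imputation in its standard form assumes missingness at random, which outcome-related removal can violate.

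**Conclusion.** The point holds in a limited form. The article grants an undefined right of termination, investigators who know the allocation hold it, and after the lavage it can serve only to end data collection. With listwise deletion implied at or below 10% dropout, removal related to the patient's course could bias the comparison despite the intention-to-treat sentence. The outcomes on days 2 and 3 and up to day 30 are the main concern; the day-1 primary markers are at risk only if the sample is missed or its value dropped.

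The size is unknown. The 19% type I error for 20 one-sided removals at +1 SD, and the wider range of 8% to 37%, are conditional illustrations and not forecasts. They require one-arm removal, a marked link to outcome and values left out of the analysis. Removal unrelated to outcome does no harm to the type I error.

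**What to change.** Replace the sentence on researchers' right of termination with wording such as:

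*Researchers may change a participant's clinical care at any time, but after randomisation only the participant's own refusal ends data collection. Data already collected are kept, and participants are followed to day 30 and analysed as assigned.*

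This sentence alone would clash with other removals after randomisation, so they must be reconciled with it and with the intention-to-treat principle: inclusion criterion (v), NSCLC confirmed by pathology after surgery; exclusion criteria (viii) and (ix), intraoperative accidents and postoperative bleeding or air leak requiring reoperation; and, under Randomization and blinding, withdrawal after emergency disclosure of allocation. For each, the protocol should say whether the patient's data continue to be collected and analysed.

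The cost is a wording amendment with ethics committee agreement and slightly more follow-up work. Trial status says that recruitment was not yet open, and follow-up of all participants is already planned. Clinicians keep full freedom over care.

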### Data management

All data recorded in the CRF will be checked twice by two independent researchers. A data management safety committee composed of three independent investigators will be needed. They will supervise the study protocol adherence and participants’ recruitment and confirm that the CRF is correctly completed and consistent with the original data. All data can be acquired only by the study investigators who have signed the confidential disclosure agreement. We do not plan to collect personal information about potential and enrolled participants beyond what is collected during normal hospitalization. After the trial, personally identifiable information will be omitted and placed in a separate database before any data analysis is performed. No participants’ data collected in this trial will be used for other ancillary studies. The adherence to the study protocol, data collection, statistical analysis, and publication issue and related safety issues will be strictly monitored by the institutional ethics committee of West China Hospital, Sichuan University.

